#### Economic Evaluation

To calculate QALYs, utility scores will be obtained from the EQ-5D-5L scores and multiplied by the duration of follow-up (12 months). The economic evaluation will be conducted from a societal perspective and will therefore include medical costs (as measured by the Institute for Medical Technology Assessment Medical Consumption Questionnaire at T1), productivity costs (as measured by the Institute for Medical Technology Assessment Productivity Cost Questionnaire at T1), and costs of the blended care intervention. Intervention program costs include GP and PN training time, time for 2 consultations in the GPC, costs for program updates, and user licenses divided by a conservative number of potential annual users. Costs for the development of the intervention as well as research-specific costs were excluded.

Incremental cost-effectiveness ratios and incremental cost-utility ratios will be calculated by comparing the costs and effects (probability of maintaining a healthy lifestyle and QALYs) of the usual care group with those of the intervention group. Statistical differences in nonnormally distributed costs and QALYs will be tested using bootstrapped 1-tailed *t* tests. A cost-effectiveness acceptability curve will be constructed with the bootstrapped incremental cost-effectiveness ratio to visualize the probability that the blended care intervention is cost-effective at specific willingness-to-pay thresholds. The ceiling ratio for the cost-utility of the interventions will be set at €20,000 (US $20,900.80) per QALY. This is an accepted Dutch cutoff point for the willingness to pay for each QALY gained by preventive interventions and is commonly used to evaluate this type of intervention in the Netherlands [46,50-52].

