**Methods:**

A parallel-group design will compare an intervention group with a waiting list control group. Participants will be nested within GPCs and randomization will occur at the GPC level. The participants in the intervention group will receive a blended care intervention. In contrast, the participants in the waiting list control group will receive care as usual for the duration of this study and will receive the online intervention afterward. All participants will be asked to complete an online questionnaire at baseline, 6 months, and 12 months after baseline, measuring self-reported adherence to lifestyle recommendations, psychosocial well-being, and quality of life. A process evaluation and cost evaluation are also included in this study. The effects will be evaluated based on differences in residual change scores between intervention and control group participants, using multilevel linear regression analyses. Moreover, effect analyses will be supplemented with Bayes factor analyses. Finally, an economic evaluation will be conducted from a societal perspective and will include medical costs, productivity costs, and costs of the blended care intervention.

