### Measurements

All participants will be asked to complete an online questionnaire at baseline, 6 months, and 12 months after baseline. GPs and PNs will not be present during the self-report questionnaire (participants will complete this assessment digitally at home). Therefore, no influence of the GP or PN on the Patient Reported Outcome Measures is expected. The questionnaires will measure self-reported lifestyle behaviors, behavioral determinants, and experienced psychological problems (see the *Outcomes* section).

The second questionnaire, administered 6 months after baseline, will also include items measuring health-related costs and, for intervention group participants only, a process evaluation questionnaire. In addition, biomedical measurements will be taken from all participants at 6 months after baseline. Blood pressure, total cholesterol/high-density lipoprotein cholesterol, and blood glucose were originally planned for the biomedical measurement. However, due to current circumstances in Dutch primary care (see the *Discussion* section), total cholesterol/high-density lipoprotein cholesterol and blood glucose measurements will be discontinued in consultation with the funding agency.

Nonresponse will be prevented by using previously effective protocols, including automated reminders 1 week and again 3 weeks after the distribution of questionnaires to patients [7,21] and email reminders to GPCs to ensure blood pressure measurement at 6 months. The quality control procedures ensure that there will be little nonresponse [8-11]. To improve the engagement of GPCs, relationships will be maintained through regular emails or phone calls to the designated contact person. In addition, a Christmas card will be sent each year on behalf of the research team. In addition, the GPCs will be offered support in patient selection and patient contact by a researcher on several occasions during this study.

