### Outcomes

#### Overview

The primary outcomes of this study are changes in lifestyle behaviors, measured by validated self-report questionnaires. PA will be assessed using the self-report Short Questionnaire to Assess Health [22,23]. Smoking behavior will be assessed using a validated (self-report) abstinence scale [24,25]. Alcohol consumption will be measured using a standardized alcohol consumption scale [26]. Dietary behavior will be assessed using a food frequency questionnaire on saturated fat intake and fruit and vegetable consumption [27-29].

Secondary outcomes are changes in experienced psychosocial problems such as anxiety and depression, fatigue, health-related QoL, and health-related costs, which will be assessed using validated self-report questionnaires. Anxiety and depression will be assessed using the Hospital Anxiety and Depression Scale [30,31]. Fatigue is assessed using the Checklist Individual Strength [32,33]. Health-related QoL is measured using the abbreviated European Organisation for Research and Treatment of Cancer Quality of Life Questionnaire [34,35]. Health-related costs are considered from a societal perspective and are measured as health care consumption in the last 3 months using the Institute for Medical Technology Assessment Medical Consumption Questionnaire, productivity losses in the last 4 weeks for both paid and unpaid labor using the Institute for Medical Technology Assessment Productivity Cost Questionnaire, and quality-adjusted life years (QALY) using the EQ-5D-5L [25,36-42]. All questionnaires used are validated, we do not conduct additional validation research as part of this research project.

Secondary outcomes are also blood pressure measurements, taken from all participants at 6 months postbaseline. Blood pressure will be assessed by clinical measurements performed by GPP.

In addition to outcome measures, relevant medical data (type of cancer, time since diagnosis, type of treatment, and recurrence) and social demographics (age, sex, level of education, income, living situation, comorbidities, and BMI), as well as intention toward PA, healthy diet, reduced alcohol consumption, and smoking cessation will be assessed at baseline. Items assessing recurrence, use of cointerventions, BMI, and lifestyle behavioral intentions will be repeated at the 6-month measurement and 12-month assessments.

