#### Sample Size

The effect evaluation of the online CAG intervention showed small to medium effect sizes (ES=0.20-0.40) on lifestyle behaviors at 6 months. In the current design, we expect an ES of 0.40 at 6 months follow-up [8]. Based on previous research on computer-tailored lifestyle interventions, we estimate an ES of 0.30 at 12 months [8,43-48]. Based on CAG data and other research in the primary care setting [49], we estimate an intracluster correlation of 0.03 to account for the multilevel design. Sample size calculation (ES=0.30; power=0.80; intracluster correlation=0.03, design effect 1.27) indicates that 282 participants are required for the effect study (141 in each condition). From 2 previous RCTs of online lifestyle interventions in patients or survivors of cancer, we know that dropout is 20%-25% [8,48]. Accounting for a 25% dropout, 376 survivors of cancer need to start in the RCT (188 per condition).

Furthermore, based on cancer prevalence figures, cancer survival rates, and the number of GPCs in the Netherlands, we expect that a standard GPC (consisting of 1-4 GPs and additional PNs) will have at least 20-40 survivors of cancer who meet the inclusion criteria. Therefore, to achieve a sufficient sample size, we aim to recruit approximately 40 GPCs, each of which will recruit 10 participants.

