### Statistical Methods

#### Overview

The first 2 steps of the analysis will test for statistical differences at baseline in lifestyle behaviors, QoL, demographics, and psychosocial and medical symptoms between the 2 study groups. Blinding of the analyst will be applied for primary outcomes. Patterns and mechanisms of missing data will be explored. Thereby, special attention will be paid to dropouts. Randomization of the GPCs should account for an even distribution between the experimental and control conditions of socioeconomic factors or other confounding factors that may skew our results. However, in case conditions are unbalanced, these factors will be adjusted for in the analysis. If necessary, other statistical adjustment procedures will be applied to minimize the impact of any bias.

Multilevel linear regression analyses will be conducted to test for differences in residual change scores between the intervention and control groups on the primary and secondary outcomes at the 6-month follow-up and the 6- and 12-month follow-up combined. Intention-to-treat (ITT) analyses with multiple imputations will be applied. Participants will be nested within GPCs to account for potential interdependence between participants. Multilevel linear regression analyses with a random intercept for GPC level will be performed to account for possible interdependence in the effect analyses. The effects on the population will be assessed via CIs.

The primary outcome measures will be the residual change scores in lifestyle behaviors, but also differences in the secondary outcomes (anxiety and depression, fatigue, [health-related] QoL, and health-related costs). Blood pressure at 6 months will be compared between the intervention and control groups. In addition, moderation analyses will be conducted to examine different potential moderators such as age, gender, type of treatment, and level of education [8-11]. Subanalyses may be performed to explore individual differences that may be attributed to the degree of participation in the intervention. Besides factors on the level of participants, factors on the level of GPCs will be considered for further analysis. Finally, process evaluation data will be analyzed and summarized descriptively.

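### QALYs are set as utility times 12 months, with no stated assessment, time weighting, baseline utility adjustment or practice-level clustering

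*Protocol article*

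**What the plan says.** The Economic Evaluation section gives one rule for QALYs: "utility scores will be obtained from the EQ-5D-5L scores and multiplied by the duration of follow-up (12 months"). No assessment time is attached to the utility, and no weighting over time is named. The comparison is given in the same section: "Statistical differences in nonnormally distributed costs and QALYs will be tested using bootstrapped 1-tailed" t tests. No covariate and no GPC effect is mentioned there. The resulting QALY difference feeds the cost-utility ratio, which is judged against a ceiling of EUR 20,000 per QALY.

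Three other places bear on the point.

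- **Schedule.** The abstract says: "All participants will be asked to complete an online questionnaire at baseline, 6 months, and 12 months after baseline". The Outcomes section lists the EQ-5D-5L among the health-related cost measures ("and quality-adjusted life years (QALY) using the EQ-5D-5L"). The Measurements section says: "The second questionnaire, administered 6 months after baseline, will also include items measuring health-related costs". The Economic Evaluation takes the medical and productivity costs from T1.
- **Imbalance.** The Statistical Methods overview says that "in case conditions are unbalanced, these factors will be adjusted for in the analysis". This stands with the multilevel effect analyses.
- **Allocation.** The Randomization section allocates GPCs by simple 1:1 randomization. The Results section reports 127 participants in 26 GPCs as of December 2024.

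**The concern.** A QALY is the area under a person's utility curve over the period. Multiplying a single follow-up utility by a full year treats that level as present from day 0. In this trial participants get access to the online program only after completing the baseline questionnaire, so there can be no effect on utility at day 0. The path from baseline through 6 to 12 months is lost.

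A second, separate issue is the comparison. A t test on QALYs adjusts for neither baseline utility nor the GPC. With few GPCs and simple randomization, the arms can easily differ in utility before treatment starts. Whatever part of that difference persists is counted as a QALY gain or loss.

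Cost-effectiveness is the stated objective of the trial, and this quantity is the denominator of its cost-utility ratio.

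**Working it through.** The article states no QALY, utility standard deviation or expected QALY gain, so there is no QALY figure to reproduce. The one related figure, the design effect, does reproduce: 1 + (10 − 1) × 0.03 = 1.27.

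**Inputs from the article.** Assessments at 0, 6 and 12 months; intracluster correlation (ICC) 0.03; 127 participants in 26 GPCs; ceiling EUR 20,000 per QALY. For the shape of an effect over time only, the Sample Size section gives "we expect an ES of 0.40 at 6 months follow-up" and "we estimate an ES of 0.30 at 12 months". These are lifestyle effects, not utility effects.

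**Assumptions.** Utility SD 0.20 (range 0.10 to 0.25); equal arms; persistence rho, the share of a baseline difference still present at follow-up when there is no treatment effect, 0.3 to 1.

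**1. Time weighting.** The trapezoidal area over one year is 0.25·u0 + 0.50·u6 + 0.25·u12. With equal baselines and the 0.40/0.30 pattern:

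0.25 × 0 + 0.50 × 0.40 + 0.25 × 0.30 = 0.275 SD-years.

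| Utility multiplied by 1 year | Result | Against 0.275 |
|---|---|---|
| 6-month value | 0.40 | +45% |
| 12-month value | 0.30 | +9% |
| mean of 6 and 12 months | 0.35 | +27% |
| equal-weight mean of 0, 6 and 12 months | 0.233 | −15% |

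For an effect that is the same at 6 and 12 months, the area is 0.75 of that effect. Either follow-up reading gives 1.00, which is 1/0.75 − 1 = +33%.

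**2. Size of a chance baseline difference.** Mean cluster size is 127/26 = 4.88, so the design effect is 1 + 3.88 × 0.03 = 1.117. With 63.5 per arm:

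SE = SD × √(2 × 1.117 / 63.5) = 0.188 × SD.

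That is 0.038 at SD 0.20 (0.019 at 0.10; 0.047 at 0.25). At the planned 141 per arm with design effect 1.27, it is √(2 × 1.27 / 141) = 0.134 SD, or 0.027 at SD 0.20. A difference of 0.03 is thus about one standard error under either sample size at SD 0.20.

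**3. What it does to QALYs.** With no treatment effect and a baseline difference d, a follow-up utility times 1 year carries rho·d. The unadjusted area carries d·(0.25 + 0.75·rho). For d = 0.03, valued at EUR 20,000:

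| rho | Follow-up utility × 1 year | EUR | Unadjusted area | EUR |
|---|---|---|---|---|
| 0.3 | 0.009 | 180 | 0.01425 | 285 |
| 0.5 | 0.015 | 300 | 0.01875 | 375 |
| 0.7 | 0.021 | 420 | 0.02325 | 465 |
| 1 | 0.030 | 600 | 0.030 | 600 |

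The area under the curve does not remove the imbalance; below rho = 1 it carries slightly more. Regression on baseline utility removes it in expectation.

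**4. Clustering.** If the ICC of 0.03 applies to QALYs, the true standard error is √1.117 = 1.06 times the one that ignores GPCs, or √1.27 = 1.13 times at the planned cluster size.

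**The case against.** The strongest reply is that the sentence is a journal condensation. It speaks of utility scores in the plural, and the full protocol or analysis plan may hold a proper weighting. In addition, the Statistical Methods overview tests baseline differences, including quality of life, and promises adjustment. It also assigns secondary outcomes, among them health-related costs, to multilevel residual-change models, and the Outcomes section groups QALYs with those costs.

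Part of this stands: the article could be read as giving QALYs two different analyses. But the Economic Evaluation section states a formula and a test of its own, which is more than leaving a detail open. The adjustment promised elsewhere is conditional on observed imbalance and is not carried into that section.

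Four stronger readings are tempting, and the documents do not support them.

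- **That the rule is biased upward.** This holds for a follow-up utility. The time point is unstated, and an equal-weight mean of all three readings errs the other way.
- **That any baseline difference becomes a QALY difference in full.** That needs rho = 1. Nor is the multiplication the cause; the missing covariate is.
- **That the EQ-5D-5L is collected only at 6 months.** The Measurements section speaks of cost items without naming the instrument, and the Outcomes section describes secondary outcomes as changes, which suggests a baseline reading.
- **That the error reverses the decision at the ceiling.** The article gives neither an expected utility gain nor an incremental cost. For an assumed constant gain of 0.03, the two methods give 0.030 and 0.0225 QALY. They fall on opposite sides of EUR 20,000 only if the incremental cost lies between 0.0225 × 20,000 = EUR 450 and 0.030 × 20,000 = EUR 600.

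**Conclusion.** The point holds as a defect in a stated rule. Utility times 12 months departs from the area under the curve on each reading examined: by +9% to +45% for follow-up readings on the protocol's own effect pattern, +33% for a constant effect, and about −15% for an equal-weight mean of three. The direction cannot be fixed from the article.

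Separately, the stated comparison leaves baseline utility and GPC clustering out. With the numbers recruited, a chance baseline difference of 0.03 is ordinary, and it would move the QALY difference by EUR 180 to 600 per person at the ceiling.

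The percentages rest on lifestyle effect sizes used only for their shape over time. The imbalance figures rest on an assumed SD, an assumed persistence, the protocol's ICC applied to utility, and equal arms.

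**What to change.** Before the analysis starts, replace the QALY sentence along these lines: each participant's QALYs are the trapezoidal area under the EQ-5D-5L utilities at baseline, 6 and 12 months (weights 0.25, 0.50 and 0.25). The incremental QALY used in the cost-utility ratio and the acceptability curve is estimated by regression with baseline utility as covariate and a GPC term, and the bootstrap resamples whole GPCs. Both parts are needed, because the area alone leaves the baseline imbalance in.

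State at which assessments the EQ-5D-5L is administered. If it is in all three questionnaires, the change costs one or two sentences and a few lines of code, with no new data. If it is collected only at 6 months, neither the area nor the baseline adjustment is possible. Because collection is expected to end by April 2025, adding the instrument now would help little, and the 12-month QALY claim should be restricted to what was measured.

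The downside is slightly more analysis work and possibly a less favorable QALY gain.

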#### Randomization

A cluster-randomized design is used, which means that randomization to either the intervention or control condition takes place at the GPC level, and that all participants in a GPC are assigned to the same condition. Neither GPCs nor participants are blinded to their assigned condition during the trial. However, during recruitment, both GPCs and the researcher are unaware of the randomization outcome to ensure that participation is not influenced by assigned conditions. The randomization outcome will be defined by a computer-generated randomization list using simple randomization (1:1), which was generated before the start of recruitment and stored with a third person.

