## Results

This study was funded in July 2020. Data collection started in August 2022 and is likely to be completed by April 2025. As of December 2024, this study is still ongoing. Data analysis is estimated to start in the spring of 2025. A total of 127 participants have been recruited across 26 GPCs in the Netherlands. The first results are expected to be published in 2026.

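### Costs and QALYs are assigned a bootstrapped 1-tailed t test with no GPC term and no stated direction, which conflicts with the multilevel analysis the article specifies for health-related costs

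*Protocol article*

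**What the plan says.** Economic Evaluation: "Statistical differences in nonnormally distributed costs and QALYs will be tested using bootstrapped 1-tailed" t tests. The section gives no direction for costs or for QALYs, no reason for using one tail, and no unit of resampling. It continues: "A cost-effectiveness acceptability curve will be constructed with the bootstrapped incremental cost-effectiveness ratio". It names no confidence intervals.

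Randomization: "randomization to either the intervention or control condition takes place at the GPC level".

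Sample Size: "Sample size calculation (ES=0.30; power=0.80; intracluster correlation=0.03, design effect 1.27) indicates that 282 participants are required for the effect study (141 in each condition"; "we aim to recruit approximately 40 GPCs, each of which will recruit 10 participants"; "Accounting for a 25% dropout, 376 survivors of cancer need to start in the RCT (188 per condition".

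Statistical Methods, Overview: multilevel regression is to be used for both primary and secondary outcomes, and the section lists health-related costs among the secondary outcomes. It adds: "Multilevel linear regression analyses with a random intercept for GPC level will be performed to account for possible interdependence in the effect analyses". The Outcomes section measures QALYs under the heading of health-related costs.

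Results: "A total of 127 participants have been recruited across 26 GPCs in the Netherlands".

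**The concern.** The design is clustered, the sample size allows for that, and the effect analyses model it. The economic evaluation then names a two-sample test that, in its ordinary form, treats participants as independent. Costs could plausibly correlate within a GPC: its own staff deliver the consultations and the usual care, and training time is incurred at GPC level. If that correlation is ignored, the bootstrap spread is too small, and both the p-values and the acceptability curve look firmer than they should.

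The single tail is a second, separate problem. The intervention arm carries extra costs for training, two consultations, updates and licences, while the Introduction hopes for lower care needs, so total cost could move either way. Whichever direction is tested, the t test cannot declare the other.

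Cost-effectiveness is the objective stated in the abstract, so these analyses are not peripheral.

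**Working it through.** **Setting the sections side by side.** Statistical Methods gives health-related costs a multilevel regression with a GPC random intercept, and effects are to be assessed through CIs. Economic Evaluation gives costs and QALYs a bootstrapped 1-tailed t test. Both cannot be the main analysis of the same outcome, and neither section refers to the other.

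**Inputs.** From the article: ICC 0.03, design effect (DE) 1.27, 40 GPCs of 10, 282 analysed participants, and 127 recruited in 26 GPCs. Assumed: alpha 0.05 (not stated); ICC 0.03 also holds for costs and QALYs (not stated; range 0.01 to 0.10 shown); equal cluster sizes; individual-level resampling.

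**The plan's own figure.** DE = 1 + (m − 1) × ICC = 1 + 9 × 0.03 = 1.27. This reproduces exactly.

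**Effect of ignoring GPC.** SE understatement = 1 − 1/√DE. True one-sided size = 1 − Φ(1.645/√DE). Widening once GPC is respected = √DE − 1.

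| Participants per GPC (m) | DE | SE too small by | True one-sided size | Widening when corrected |
|---|---|---|---|---|
| 127/26 = 4.88 (recruited) | 1 + 3.88 × 0.03 = 1.117 | 5.4% | 6.0% | 5.7% |
| 282/40 = 7.05 (planned, analysed) | 1 + 6.05 × 0.03 = 1.18 | 8.0% | 6.5% | 8.7% |
| 10 (planned, recruited) | 1.27 | 11.3% | 7.2% | 12.7% |

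Over ICC 0.01 to 0.10 the size runs from 5.3% to 8.1% at m = 4.88, and from 5.8% to 11.6% at m = 10.

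**Check with skewed costs.** In 20,000 simulated trials per setting, lognormal costs were analysed with an individual-level 1-tailed Welch t test (not bootstrapped). With ICC 0.03 set on the log scale, the size was 5.5% (26 GPCs × 5), 5.7% (40 × 7) and 6.5% (40 × 10). These are lower than in the table because the ICC on the cost scale is then (e^0.03 − 1)/(e − 1) = 0.018. A t test on GPC means gave 4.7 to 4.9% in the same settings.

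**Sidedness.** At alpha 0.05 one tail uses a critical value of 1.645, against 1.960 for two sides. The error allowed in the tested direction is 5% rather than 2.5%, and nothing can be declared in the other direction. This holds whatever the unit of resampling.

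**Choice of bootstrap.** A plain two-stage bootstrap (GPCs, then participants) is not a safe replacement. Take 13 GPCs of 5 in one arm, total variance 1 and ICC 0.03:

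- Between-GPC variance is 0.03, and within-GPC variance divided by m is 0.97/5 = 0.194.
- The true variance of the arm mean, times 13, is 0.03 + 0.194 = 0.224.
- The two-stage bootstrap gives 0.224 × 12/13 + 0.194 × 4/5 = 0.207 + 0.155 = 0.362. The SE ratio is √(0.362/0.224) = 1.27, so it is 27% too large.
- Resampling whole GPCs only gives √(12/13) = 0.961, so it is about 4% too small.

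**The case against.** The strongest reply is that the Economic Evaluation section never says participants are treated as independent. A bootstrap can resample GPCs, nothing excludes that, and a condensed article may leave such detail to an analysis plan. This stands: a reader might infer that the plan definitely ignores the clustering, but that follows only from the name of the test and from silence on the resampling unit. What silence does not explain is the conflict: the article puts costs under a multilevel model in one section and names a t test for them in another.

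Two other stronger readings also go too far. A reader might say the plan's confidence intervals are too narrow, but this section states none. The narrowing applies, conditionally, to the bootstrap distribution and the acceptability curve. A reader might also say that only one direction can be found in the whole economic evaluation. The limit applies to the t tests alone: the cost-effectiveness and cost-utility ratios and the curve can show higher costs or a QALY loss. Nor is it known that the untested direction is a cost increase, since no direction is given.

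It is also fair to say that the clustering error is modest at the recruited cluster size, and that setting 7.2% against 2.5% per direction would mix two separate problems. The larger sizes, up to 11.6%, need an ICC of 0.10, which the article does not support.

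**Conclusion.** The point holds in a limited form. Two things rest on stated text: the 1-tailed test without a direction, and the conflict between the two sections on how costs are analysed. The named test, taken as written, does not fit randomization by GPC.

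The numerical consequence is conditional. With individual resampling, ICC 0.03 for costs and QALYs and alpha 0.05, the SE is about 5% too small at current recruitment (size 6.0%), 8% at 7 per GPC (6.5%) and 11% at 10 per GPC (7.2%). Unequal GPC sizes would raise these figures, and dropout from the 127 would lower them. The acceptability curve would be too certain to a matching degree. The lifestyle outcomes, which are primary, are not affected, because their model includes the GPC random intercept.

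**What to change.** Reconcile the Statistical Methods and Economic Evaluation sections so that costs and QALYs have one stated analysis that respects GPC. Either of these would do:

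- a bivariate multilevel model for costs and QALYs with a GPC random effect; or
- a bootstrap that resamples whole GPCs within each arm and keeps each person's costs and QALYs paired.

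Use a two-stage bootstrap only with a shrinkage correction, because the plain version overstates the SE by about 27% at these cluster sizes. Drop the 1-tailed tests and report two-sided 95% confidence intervals for the differences in costs and QALYs. Build the cost-effectiveness plane and the acceptability curve from the same replicates or model.

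The cost is a changed analysis script, with no new data. Intervals become about 6 to 13% wider at ICC 0.03, before the change from one to two sides. With about 13 GPCs per arm (26 split evenly, which simple randomization does not guarantee), the GPC-level bootstrap still understates the SE by about 4%, and this should be acknowledged in the report.
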